### Sites

The University of Iowa serves as the primary site for the ChANGE-HD study and received IRB approval from the WCG to begin recruitment on 11/18/2019. Four additional sites were added, including the Children’s Hospital of Philadelphia (CHOP), Columbia University, the University of Texas at Houston, and the University of California, Davis. Site were approved for recruitment by WCG on 11/16/2020, 11/16/2020, 5/12/2020, and 4/16/2020, respectively. Vanderbilt University was added to the study and received approval to recruit participants on 11/14/2024.

### Study period and recruitment goals

ChANGE-HD was originally planned as a 5-year study, aiming to complete 1,500 assessments of 400 participants by the end of the fifth year. However, the COVID-19 pandemic delayed study progress by causing significant disruptions in recruitment and scheduling across the five original study sites and required us to update our timelines after Year 2 (Table 3). As a result, the assessment period, including pre-COVID data collection, was extended to approximately seven years and our recruitment targets were changed to 450 participants across 1,030 assessments. Note that the extension allowed for the inclusion of new baseline visits, as well as additional repeat visits for those already enrolled. Actual recruitment values by site and year are shown in Table 4. Despite the disruptions of COVID-19, our most recent power analysis shows that we are still on track to achieve our study aims (see *Power analysis and sample size calculation*).

**Table 3 pone.0336088.t003:** Study timeline and recruitment targets. Numbers represent the targeted number of subjects and assessments, respectively.

	Year 1 ‘19‐20	Year 2 ’20‐21	Year 3 ’21‐22	Year 4 ’22‐23	Year 5 ’23‐24	Year 6 ’24‐25	Year 7 ’25‐26	Cumulative Total Target
**Target Total**	50/200	80/300	110/400	110/400	50/200			400/1500
**Revised Target after Year 1**		80/300	107/400	107/400	106/400			400/1500
**Revised Target after Year 2**		30/100	80/300	110/400	100/400	80/300		400/1500
**Revised Target after Year 3**		30/100	80/200	100/200	100/200	100/200	40/130	450/1030

**Table 4 pone.0336088.t004:** Recruitment by Site and Year. * - As of 02/20/2026.

	2020	2021	2022	2023	2024	2025	2026*	Total Recruitment
**The University of Iowa**	28	43	36	49	62	77	7	**302**
**CHOP**	3	10	27	40	44	55	8	**187**
**Columbia University**	7	16	26	19	27	24	0	**119**
**UT Houston**	0	13	36	38	30	36	0	**153**
**UC, Davis**	9	4	22	26	33	18	0	**112**
**Vanderbilt University**	0	0	0	0	63	63	5	**131**
**Cumulative Total**	**47**	**133**	**280**	**452**	**711**	**984**	**1004**	**1004**

### Participants

At baseline, approximately 450 total participants will be enrolled across all sites. Although annual visits are not required for an ALD design, retention is best with close follow-up, and subjects are asked to return annually. We aim to recruit an even distribution of subjects across age groups, with 225 participants in the range of 6–18 years-old and the remaining participants in the range of 19–30 years-old.

Inclusion criteria:

Between 6–30 years oldFluent in EnglishHave a biological parent or grandparent who has been genetically or clinically diagnosed with HD, indicating that the participant is at risk for HD (determined from participant or family report)Demonstrate an age-appropriate understanding of HD and its risks (If the parents indicate that their child is unaware, we will not enroll the participant until an age-appropriate discussion has occurred)

Exclusion criteria:

A history of medical diagnoses that could potentially confound the study results (e.g., major head trauma, seizures, tumors, or any other major medical illness requiring ongoing care). If an aspect of their medical history obscures their symptoms as being directly attributable to HD (e.g., a concomitant congenital disorder) they are excluded from participation.Have Juvenile-onset HD (JOHD)MRI contraindications. Participants of childbearing potential must undergo a urine pregnancy test before their MRI. If positive, they are excluded from the MRI but may still complete other assessments.Manifestation of overt motor features of HD. This is ascertained by reporting from parents (or participants themselves if they are over 18) during a screening visit. If the participant or the parent reports that they are currently manifesting any motor symptom of HD, the participant is referred to a child or adult neurologist for clinical evaluation. These individuals are also invited to participate in the JOHD study if they were diagnosed with JOHD before the age of 21 (see below).

Participant recruitment is conducted across the United States. Potential participants along with their parents or grandparents are identified through local hospital or clinic records and HD registries. Recruitment platforms such as *Research Match*, *HD Trial Finder*, and *ClinicalTrials.gov* are used to share study information with the community. Additionally, study-dedicated social media channels and websites are maintained to disseminate updates. The study is also advertised through events, newsletters, social media, and websites of national HD organizations, including the HDSA, its state chapters, Help4HD International, National Youth Alliance (NYA) of HDSA, HDYO, and the Huntington Study Group (HSG).

### Power analysis and sample size calculation

Based on our findings from the Kids-HD sample, our central hypothesis is that GE participants will demonstrate altered trajectories in general brain size and cognition across YTO. Specifically, we predicted that GE individuals will demonstrate significantly larger brain volume (primary outcome measure) and stronger cognition scores (secondary outcome measures) prior to 20 YTO and significantly smaller brain volume and weaker cognition between 20−0 YTO. Using our updated recruitment target of 1,030 assessments across 450 participants, we estimated at least 90% power to reproduce our previous findings at p = .01 (except for cortical thickness; Table 5). Note that Table 5, which shows the results of our power analysis, includes functional and structural measures, but that our power analysis is primarily based on the structural findings from Kids-HD. Assuming 40% of participants are GE (as in the previous study), we can assume at least 400 visits from 180 unique genetically affected participants. The power analysis used the Kids-HD sample from Neema et al. (2024), and was based on 136 visits from 79 gene-expanded participants. Because the mean number of visits (and hence, statistical information) per participant will be higher in ChANGE-HD, a conservative estimate of the overall increase in statistical information (i.e., log-likelihood statistics) is obtained from the ratio of unique participants, which is 2.278. If the findings from Kids-HD hold, then the expected values of the analogous F statistics (Table 5) will increase by at least 2.278-fold. Standard power calculations using these projected F statistics yield results that exceed the above-claimed minimum statistical power.

**Table 5 pone.0336088.t005:** Tests used for hypotheses and power analysis (from Neema et al., 2024).

		Kids-HD				Change-HD		
**Measures**	**N**	**ndf**	**ddf**	**F**	**p**	**Projected F**	**Projected NCP**	**Power**
General Ability Index**	136	1	87.66	13.50	<0.001	30.78	29.445	0.997
Behavior composite**	135	2	120.27	10.91	<0.001	24.87	47.343	>0.999
PANESS**	128	1	46.12	8.92	0.005	20.34	18.933	0.956
Whole brain*	117	3	62.63	7.79	<0.001	17.76	49.491	>0.999
Cerebrum	117	3	62.55	7.80	<0.001	17.78	49.557	>0.999
Cortical gray matter*	117	1	99.90	12.22	<0.001	27.86	26.593	0.995
Cortical surface area	117	1	95.22	12.17	<0.001	27.75	26.468	0.994
Cortical thickness*	117	1	54.67	2.95	0.091	6.73	5.612	0.406
Cortical folding index	117	3	82.04	5.54	0.002	12.63	34.455	0.996
Cortical curvature index	117	1	62.27	10.49	0.002	23.92	22.559	0.983
Cerebral white matter*	117	3	51.46	9.84	<0.001	22.44	63.099	>0.999
Cerebellum	117	2	74.95	9.67	<0.001	22.05	41.540	>0.999
Striatum	117	5	102.37	13.98	<0.001	31.87	152.867	>0.999
Globus pallidus	117	5	80.15	16.22	<0.001	36.98	177.722	>0.999
Thalamus	117	1	102.87	7.47	0.007	17.03	15.871	0.916

Non-centrality parameter (NCP) is calculated from an F statistic by NCP = (F-(2F/ddf)-1)*ndf. These non-centrality parameters (NCP) refer to non-central chi-square distributions with the corresponding number of degrees of freedom. These are the large sample approximate distributions of the maximum likelihood test statistics under the minimum differences that cause rejection of the null hypothesis. These NCP values are a function of this minimum required difference and the contribution per participant to the analysis test statistic. ddf = denominator degrees-of-freedom, ndf = numerator degrees of freedom. * - primary outcome measures, ** - secondary outcome measures.

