
### Beyond Kids-HD: Embracing a new era with ChANGE-HD

While the Kids-HD study provided novel insights, it also raised several critical questions that required further investigation. Kids-HD’s modest single-site sample (202 GE children) produced valuable data but required a necessary expansion for greater reliability and broader application. This prompted the launch of the NIH-funded, multi-site ChANGE-HD study in 2019, which builds upon the Kids-HD findings and addresses the following key areas:

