
#### Statistical analysis using YTO Models.

We will employ a YTO model, which provides a more detailed representation of disease-related changes (between 50 and 0 YTO) than an age-based analysis [15,16,18,23]. Our statistical analyses are derived from Langbehn et al. [80] and our own work [17] investigating neural and behavioral changes across YTO. This method is based primarily on data from individuals with CAG repeats between 41 and 56 [80] but extrapolation has generalized usefully to CAG repeats extending beyond this range (40, 57–70, etc.) [17]. Because individuals with between 36–39 CAG repeats represent an incomplete penetrance group, they will be excluded from the YTO analysis and will be examined separately in exploratory analyses. Individuals with >70 CAG repeats will also be excluded as they are likely to have already begun showing motor symptoms of HD and are likely classified as patients with JOHD. All hypotheses relate to either systematic group difference between GE and GNE individuals or to differences within the GE group driven by CAG expansion length and age (or years to onset as in the NfL analysis). Our analysis approach will include the following steps: 1) age and sex correction based on the data from healthy controls, 2), estimation of YTO, and 3) YTO modeling with testing for potential additional sex differences and sex by YTO interactions.

For each dependent variable, we apply statistical corrections to separate developmental effects of typical aging from those experienced by GE individuals as part of the disease trajectory. We perform this correction by modeling age and sex effects in GNE controls using a regression that includes within-subject and within-family random effects. The models incorporate both linear and potential non-linear age relationships. Nonlinearity is modeled flexibly via restricted cubic splines (“natural splines”). The degree of non-linearity (up to five degrees of freedom) is determined by choosing the model with the lowest Akaike Information Criterion (AIC), with tied AIC values (≤ 1.0) favoring the simpler model. We also test the model for sex and sex-by-age interactions, which are excluded from the final model if found to be nonsignificant. The fitted values for this model are then subtracted from the dependent value to complete the correction.

Estimation of age of motor symptom onset is calculated using the Langbehn model [80] shown below:

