To assess the relationship between age- and sex-adjusted neuroimaging variables (e.g., cortical grey and white matter volume, striatal volume, corticostriatal structural and functional connectivity, etc.) and clinical outcomes in GE individuals, we apply modeling techniques as described above. The models include random effects of subject and family, but exclude age and sex, as the values will have already been corrected using the data from GNE participants. Imaging measures are generally predictor variables, and clinical measures are the outcomes, reflecting the potential causal relationships between the two measurement classes. As in our previous work [17], we also split our GE participants into two groups with a cutoff of 20 YTO and test for differences in the imaging versus clinical relationships. This is based empirically on our work [17] showing divergence in neural and behavioral measures at this point in the YTO trajectory and because of work showing an upward trend in NfL at 20 YTO [18]. As described above, potential non-linear relationships between biomarkers and clinical measures are interrogated using restricted cubic splines (up to five degrees of freedom). For all analyses, a *p* value of < 0.05 is considered statistically significant.

In addition to our hypothesis-driven analyses, we also plan to perform detailed exploratory analyses to uncover novel neuroimaging biomarkers that both distinguish GE and GNE individuals and individuals with variations in HD-related single nucleotide polymorphisms (SNPs). For example, machine learning approaches, such as deep learning, have been applied to neuroimaging data from patients with neurodegenerative disorders to identify how those SNPs affect brain anatomy and function [81]. As mentioned above, SNPs in several genes explain variation in the eventual onset of motor symptoms in HD [32–34]. Using deep learning and other machine learning approaches as exploratory tools may reveal new mechanistic information about how these SNPs shape neurodevelopment and -degeneration.

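### Table 5 scales the whole F statistic instead of the non-centrality parameter, so power is overstated throughout and the 90% statement fails for one further measure, the thalamus

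*Protocol article*

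**What the plan says.** The section on power and sample size (Protocol article) makes this claim: "we estimated at least 90% power to reproduce our previous findings at p = .01 (except for cortical thickness; Table 5"). It reaches it in three steps.

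- The number of gene-expanded (GE) participants: "Assuming 40% of participants are GE (as in the previous study), we can assume at least 400 visits from 180 unique genetically affected participants". This is 40% of 450, with nothing deducted.
- The ratio of these 180 to the 79 Kids-HD GE participants behind the source analysis, 2.278, is taken as a conservative measure of the gain in statistical information, because visits per participant will be higher.
- The ratio is applied to F: "then the expected values of the analogous F statistics (Table 5) will increase by at least 2.278-fold". The note to Table 5 then converts the projected F with NCP = (F - 2F/ddf - 1) x ndf.

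The section on study period and recruitment goals relies on this analysis when it says the study is still on track at the revised target of 450 participants and 1,030 assessments.

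GE is defined under Biological samples as 36 or more repeats. The section on YTO models says of participants with 36-39 repeats that "they will be excluded from the YTO analysis and will be examined separately in exploratory analyses", and also excludes those with more than 70.

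**The concern.** The formula in the table note treats the expected F as a null part of about 1 plus NCP/ndf. More participants enlarge the NCP and leave the null part alone. If F is multiplied first and 1 subtracted afterwards, the null part is scaled up too and most of that inflation is counted as signal. Power is then overstated in every row, most visibly where the Kids-HD F was small. At stake are the accuracy of the 90% statement and how far it can support the assurance about the reduced target.

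A second, separate question is whether the two sides of the ratio count the same kind of participant. The 180 are all GE participants expected to enrol, while the YTO analysis being powered leaves some of them out.

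**Working it through.** **Inputs** (Power analysis section and Table 5): ratio r = 180/79 = 2.2785; alpha = .01; ndf, ddf and F by row.

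**Reproducing the plan.** Projected F = r x F, ddf' = r x ddf, NCP = (rF - 2rF/ddf' - 1) x ndf, and power from the non-central F(ndf, ddf', NCP) at .01. For the thalamus (ndf 1, ddf 102.87, F 7.47):

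- rF = 17.02 (printed 17.03, which matches a ratio rounded to 2.28)
- NCP = 17.02 - 0.145 - 1 = 15.87 (printed 15.871)
- power = 0.916 (printed 0.916)

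PANESS (0.956), curvature (0.983), cortical gray matter (0.995) and thickness (0.406) reproduce as well, so this is how the table was built.

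**Scaling the NCP instead.** NCP0 = (F - 2F/ddf - 1) x ndf from the Kids-HD F; then NCP = r x NCP0, with the same power function. For the thalamus:

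- NCP0 = 7.47 - 0.145 - 1 = 6.325
- r x NCP0 = 14.41
- power = 0.884 (0.889 with a non-central chi-square, 0.877 with ddf left unscaled)

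All three variants are below 0.90. Expected F rises by (1 + 2.278 x 6.325)/(1 + 6.325) = 2.10-fold, not at least 2.278-fold.

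**Size of the excess.** Printed minus rescaled NCP is ndf x (r - 1) x (1 + 2F/ddf). That is 1.28 x ndf plus a small ddf term; for the thalamus, 1.278 x 1.145 = 1.46.

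| Measure | Status | NCP0 | NCP printed | NCP rescaled | Power printed | Power rescaled |
|---|---|---|---|---|---|---|
| Thalamus | neither | 6.33 | 15.87 | 14.41 | 0.916 | **0.884** |
| Cortical thickness | primary | 1.84 | 5.61 | 4.20 | 0.406 | 0.290 |
| PANESS | secondary | 7.53 | 18.93 | 17.16 | 0.956 | 0.933 |
| Curvature index | neither | 9.15 | 22.56 | 20.86 | 0.983 | 0.974 |
| Folding index | neither | 13.22 | 34.46 | 30.11 | 0.996 | 0.988 |
| Surface area | neither | 10.91 | 26.47 | 24.87 | 0.994 | 0.991 |
| Cortical gray matter | primary | 10.98 | 26.59 | 25.01 | 0.995 | 0.992 |
| General Ability Index | secondary | 12.19 | 29.45 | 27.78 | 0.997 | 0.996 |

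The other rows, including the primary measures whole brain and cerebral white matter, stay above 0.999.

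**What restores 90% for the thalamus.** 188 GE participants give 0.899 and 189 give 0.901. As a ratio, about 2.385 is enough, 5% above 2.278. If information grew fully with visits (400/136 = 2.94), power would be 0.957.

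**The count of 180.** The article does not give the share of GE participants outside 40-70 repeats, so the losses below are assumptions. The GE count is reduced and the 79 held fixed.

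| Assumed loss | GE left | Thalamus, plan's method | Thalamus, NCP scaled | PANESS, NCP scaled |
|---|---|---|---|---|
| 5% | 171 | 0.898 | 0.864 | 0.919 |
| 10% | 162 | 0.877 | 0.841 | 0.901 |
| 20% | 144 | 0.822 | 0.785 | 0.855 |

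In the other direction, if 50% of the 450 were GE (225), thalamus power with the NCP scaled would be 0.950.

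**The case against.** **The observed effect could be taken at face value.** The projection is conditional on the Kids-HD findings holding. If the true NCP is set to the observed F x ndf with no bias correction, the new NCP for the thalamus is 2.278 x 7.47 = 17.02, power is 0.936, and the printed 15.87 looks cautious. That is a coherent choice, but Table 5 does not make it. Its note subtracts the null part, and once that is done it has to come off before scaling.

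**The ratio ignores extra visits.** Planned visits per GE participant are 400/180 = 2.22 against 136/79 = 1.72 in Kids-HD, and a 5% gain in information would bring the thalamus back to 90%. This stands as a reason to expect true power above 0.884. The article names the cushion without quantifying it, and the printed figures do not use it.

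**The consequence is small.** This stands. One unstarred measure crosses 90%, by 1.6 points, and thickness was already excepted. The analysis section sets significance at a p "value of < 0.05 is considered statistically significant"; at that level the rescaled thalamus power is 0.966.

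**The two sides of the ratio may already match.** The YTO section says the model was extended in the source analysis to 40 and 57-70 repeats, which suggests that the 79 were restricted in the same way. If the 40% is also a share after that restriction, the ratio does not change. The article does not say.

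**Stronger readings a reader might infer.** Kids-HD is described as a "modest single-site sample (202 GE children"), and 79/202 is 39%, so one might expect only about 70 of the 180 to be analysable and power to collapse. The documents do not explain the gap between 202 and 79, and nothing says ChANGE-HD would repeat it. Likewise 202/406 = 50% might seem to expose the 40% as a flattering assumption. A higher GE share would raise power, and the article also mentions a comparison group with no family link to HD, so 406 may not be the at-risk denominator.

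**Conclusion.** The scaling error is confirmed from the plan's own formula, ratio and inputs. All projected NCPs in Table 5 are too high. The statement of at least 90% power except for cortical thickness is not met for the thalamus (0.884 at 180 GE participants), and the power for thickness, a primary measure, is 0.290, not 0.406. These figures assume the participant ratio of 2.278, alpha .01 and no credit for extra visits.

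It would be wrong to conclude that the study is underpowered for its central hypothesis. The primary measures other than thickness keep more than 0.99, PANESS keeps 0.933 and the other starred secondary measures keep at least 0.996. The thalamus is neither primary nor secondary.

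The mismatch between the GE definition and the YTO exclusions is a real gap in the description, as is the unexplained 40%. Neither the size nor the direction of their effect on power is established.

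**What to change.** - Recompute Table 5 with projected NCP = ratio x Kids-HD NCP, and correct the sentence about the F statistics.
- Then either restate the claim as about 88% or more except for cortical thickness (29%), or calculate and justify a larger information ratio from the additional visits and use it throughout the table. Full visit scaling gives the thalamus 0.957.
- Put both sides of 180/79 on the same basis: participants with 40-70 repeats who are eligible for the YTO analysis. An aggregate count is enough and unblinds nobody.
- State where the 40% GE share comes from and how it relates to the 202 GE children and 406 individuals reported for Kids-HD.

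The cost is a recalculation and a slightly less favourable published figure. The primary measures need no change to design or enrolment. For the thalamus alone, 90% without credit for visits would need 189 GE participants.

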#### Cognitive, behavioral, environmental, and motor measures.

As mentioned previously, the clinical assessment protocol is modeled after the ABCD Study [31], which tracked healthy children (9–10 years old) through adolescence. Although we are studying individuals who are both younger (6–9 years old) and older (25–30 years old), the ABCD study provides the gold standard model for large-scale studies of children and adolescents, which make up a large segment of our population of interest. Table 6 details the full assessment battery, including measures of cognition, behavioral health, environment & health, and motor function.

**Table 6 pone.0336088.t006:** ChANGE-HD assessments. MTTC = Maximum time to complete in minutes.

Domain	Test Name	Construct	MTTC	Digital	Validated Age Range/ Administered Ages
**Cognitive**	NIH Toolbox – Picture Vocabulary [45]	Language	4	Yes	• 3-85/ 6-30
	NIH Toolbox – Oral Reading Recognition [45]	Language	3	Yes	• 7-85/ 6 −30
	NIH Toolbox – Dimensional Change Task [45]	Executive function	4	Yes	• 3-85/ 6-30
	NIH Toolbox – Flanker Inhibitory Control [45]	Attention	3	Yes	• 3-85/ 6-30
	NIH Toolbox – List Sorting Working Memory [45]	Working memory	7	Yes	• 7-85/ 6-30
	NIH Toolbox – Picture Sequence Memory [45]	Episodic memory	7	Yes	• 3-85/ 6-30
	NIH Toolbox – Pattern Comparison Processing Test [45]	Processing speed	3	Yes	• 7-85/ 6-30
	NIH Toolbox – Rey Auditory Verbal Learning Task [45]	Verbal memory	3	Yes	• 8-85/ 6-30
	Controlled Oral Word Association [46]	Verbal fluency	5	No	• 6-69/ 6-30
**Motor**	Unified Huntington’s Disease Rating Scale (UHDRS) [47]	Motor	10-15	No	• 11 + / 6-30
	NIH Toolbox – 9-hole Pegboard Task [48]	Dexterity	4	Yes	• 3-85/ 6-30
	Quantitative-Motor [49]	Motor	45	Yes	• 6 + / 6-30
**Behavioral**	Achenbach System of Empirically Based Assessment [50]	Adaptive and maladaptive functioning	20	Yes	• Child Behavior Checklist Validated ages: 6–18 ◦ Administered ages: 6–17 ◦ Parent’s report • Youth Self-Report ◦ Validated ages: 11–18 ◦ Administered ages: 11–17 • Adult Behavior Checklist ◦ Validated ages: 18–59 ◦ Administered ages: 18–30 • Adult Self-Report ◦ Validated ages: 18–59 ◦ Administered ages: 18–30
	Urgency, Premeditation, Perseverance, Sensation Seeking, and Positive Urgency (UPPS-P) Behavior Scale [51,52]	Impulsivity	5	Yes	• Short version ◦ Validated ages: 14–72 ◦ Administered ages: 12–30 • Children’s version ◦ Validated ages: 7–13 ◦ Administered ages: 6–11

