In the Kids-HD study, cognitive evaluation relied heavily on the Wechsler scales. However, in alignment with new NIH guidelines seeking to improve the inter-rater reliability of multi-site cognitive outcomes, a protocol change was implemented to use the NIH Toolbox (Version 2) [45]. The NIH Toolbox is an iPad-based assessment tool designed to obtain comprehensive metrics from a single visit in the following domains: language, verbal fluency, executive function, attention, working memory, episodic memory, processing speed, and visuospatial intelligence. It offers several advantages, including being digital, standardized, and comprehensive, reducing variability in test results, improving the precision of cognitive measurements, and enabling comparisons across diverse ages and sites. The NIH Toolbox is also validated for use in individuals across the lifespan (ages 3–85; [45,48,59]) and is widely used to study neurological disorders and diseases, such as stroke [60] and Huntington’s disease [61,62], and other clinical populations [63]. Critically, the NIH Toolbox provides a domain-specific score based on all cognitive tests. These standardized cognitive domain scores will serve as our primary metric to assess cognitive function, although we will also explore the effects of gene expansion on each individual test.

Motor functions are assessed using the Unified Huntington’s Disease Rating Scale (UHDRS) motor battery, the NIH Toolbox Nine Hole Peg Test, and the Quantitative Motor (Q-Motor; primary outcome measure for motor performance) assessment. The Q-Motor battery assesses tapping speed and regularity of movements produced by index fingers, hands, and feet. It also quantifies grasping, lifting, and involuntary choreiform movements. The Q-Motor battery is also likely to be more sensitive to pre-manifest changes in motor performance than the UHDRS-TMS [64]. Altogether, it provides a comprehensive and precise evaluation of motor function that has been validated in children [30].

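### Table 5 gives ChANGE-HD power for General Ability Index and PANESS as secondary outcomes, but neither is in the study's battery, and power for the measures that replace them is not established

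*Protocol article*

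**What the plan says.** In *Power analysis and sample size calculation*, Table 5 puts a double asterisk on three rows: "General Ability Index", Behavior composite and PANESS. The footnote defines that mark as a secondary outcome. Each row carries projected F, non-centrality parameter (NCP) and power in the ChANGE-HD columns; power is 0.997 for General Ability Index and 0.956 for PANESS. The text above the table claims "we estimated at least 90% power to reproduce our previous findings at p = .01 (except for cortical thickness; Table 5", so cortical thickness is the only exemption.

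In *Cognitive, behavioral, environmental, and motor measures*, the article states "Table 6 details the full assessment battery, including measures of cognition, behavioral health, environment & health, and motor function". The cognitive tests in Table 6 are NIH Toolbox tests and Controlled Oral Word Association. The motor tests are the UHDRS, the 9-hole pegboard and Q-Motor. The same section reports that Kids-HD leaned on the Wechsler scales and that "a protocol change was implemented to use the NIH Toolbox (Version 2". It makes the Toolbox domain scores the main cognitive metric and Q-Motor the primary measure of motor performance.

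**The concern.** The article gives two different answers to what its cognitive and motor outcomes are. Table 5 names two measures and states how well the study can detect effects on them. The assessment section names others, which have no power figure. A reader who takes Table 5 at face value will believe that the cognitive and motor outcomes have at least 95% power, when those figures concern tests that ChANGE-HD does not list.

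Cognition matters most here, because the central hypothesis in the power section concerns brain size and cognition across years to onset. The projection takes Kids-HD F statistics and inflates them for sample size. That carries over only if the outcome keeps the same standardised effect and reliability. When the instrument changes, this becomes an extra assumption, and the article neither states nor supports it. The mismatch also leaves the starred outcomes to be settled later among several Toolbox domain scores and many Q-Motor parameters.

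**Working it through.** **1. Tables side by side.** General Ability Index appears in Table 5 and otherwise only as a past Kids-HD result in Table 1. PANESS appears in Table 5 and nowhere else in the article. Neither is in any domain of Table 6. NIH Toolbox domain scores and Q-Motor are in the assessment section and have no row in Table 5.

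**2. Inputs to the projection**, all from the power section:
- Target: "Using our updated recruitment target of 1,030 assessments across 450 participants".
- Gene-expanded share: "we can assume at least 400 visits from 180 unique genetically affected participants" (40% of 450 = 180).
- Kids-HD base: the analysis "was based on 136 visits from 79 gene-expanded participants".
- Information ratio: 180/79 = 2.278.
- General Ability Index: ndf 1, ddf 87.66, F 13.50. PANESS: ndf 1, ddf 46.12, F 8.92.
- NCP = (F − 2F/ddf − 1) × ndf, alpha 0.01.

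**3. Reproducing the stated figures.** Both F and ddf are scaled by 2.278.
- General Ability Index: F = 13.50 × 2.278 = 30.753; ddf = 87.66 × 2.278 = 199.69; NCP = 30.753 − 2(30.753)/199.69 − 1 = 29.445 (stated 29.445). Power from the non-central F is 0.997 (stated 0.997).
- PANESS: F = 8.92 × 2.278 = 20.320; ddf = 46.12 × 2.278 = 105.06; NCP = 20.320 − 2(20.320)/105.06 − 1 = 18.933 (stated 18.933). Power is 0.956 (stated 0.956). With unscaled ddf it is 0.947; with the non-central chi-square it is 0.962.

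The arithmetic is sound. The question is only which outcomes the figures describe.

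**4. What a change of instrument could do.** The article gives no effect size for the Toolbox domain scores or Q-Motor, so no single corrected figure exists. Let k be the ratio of the replacement's standardised effect to the Kids-HD effect. This k is an assumption, not a document figure. The NCP becomes NCP × k², with ndf and scaled ddf unchanged. For k = 0.8 the NCPs are 29.445 × 0.64 = 18.845 and 18.933 × 0.64 = 12.117. Power at alpha 0.01:

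| k (assumed) | In place of General Ability Index | In place of PANESS |
|---|---|---|
| 1.0 | 0.997 | 0.956 |
| 0.9 | 0.988 | 0.899 |
| 0.8 | 0.958 | 0.802 |
| 0.7 | 0.883 | 0.663 |
| 0.6 | 0.743 | 0.497 |
| 0.5 | 0.546 | 0.332 |

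Power equals 90% at k of about 0.72 for General Ability Index and about 0.90 for PANESS. If k exceeds 1, power is higher than stated.

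**The case against.** The best defence is that the article is open about the change. It discloses the move to the NIH Toolbox and names the new lead measures. Table 5 is captioned as coming from the Kids-HD publication, and the text says that the power analysis rests mainly on structural results and is conditional on the Kids-HD findings holding. The hypothesis itself speaks of cognition scores, not of General Ability Index. The list of expected biomarkers at the end of *Beyond Kids-HD* narrows the field to general intelligence, processing speed, tapping variability, grip force and repetitive movements. Choosing the exact score is often left to a SAP.

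Much of this stands, and it rules out several stronger readings that a reader might infer:
- *That the cognitive and motor questions cannot be analysed.* Only the two named measures are absent; both domains are assessed by other instruments.
- *That a motor hypothesis central to the study is lost.* The central hypothesis in the power section covers brain size and cognition. Motor function enters that section only through the PANESS row.
- *That power for the replacements is below 90%.* The documents do not show this. The article expects Q-Motor to be more sensitive to pre-manifest change than the UHDRS motor score. At the 0.05 level used in the analysis section, power is also less fragile: with k = 0.8 it is 0.991 and 0.932.

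The caveats do not remove the secondary-outcome labels, the ChANGE-HD power columns or a 90% claim that exempts cortical thickness alone. No text links General Ability Index to a Toolbox score or PANESS to a Q-Motor score. Nor is this a detail left to a SAP: the article states outcomes that its own full battery does not contain. The supplementary S2 Table is not shown, but the article itself describes Table 6 as complete.

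**Conclusion.** The point holds as an internal contradiction with a misattributed power claim. Two of the three starred secondary outcomes are not collected under those names, and their stated power belongs to Kids-HD instruments. Power for the measures actually collected is unestablished; the margin before it falls below 90% at alpha 0.01 is wide for the cognitive row (k down to about 0.72) and thin for the motor row (about 0.90). Those thresholds rest on the assumed ratio k, on the Kids-HD effects being true, and on the replacement models keeping one numerator degree of freedom. The conclusion does not depend on which test General Ability Index is derived from, which the article does not say. Power for the structural MRI outcomes, including the starred primary ones, and the target of 450 participants and 1,030 assessments are untouched. The Behavior composite row is outside this point.

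**What to change.** In *Power analysis and sample size calculation* and Table 5:

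1. Make the starred cognitive and motor outcomes match the assessment section: one specified NIH Toolbox score and one specified Q-Motor score, fixed before any genotype-linked analysis.
2. Keep the General Ability Index and PANESS rows only if they are marked as Kids-HD measures whose power is not carried over to the new instruments.
3. Withdraw the claim of at least 90% power for cognitive and motor outcomes. If a figure is wanted there, state the assumed effect ratio and show a range such as the one above.

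This is a change of wording and needs no new data or larger sample. The cost is that the article gives up its stated power for these two secondary outcomes.
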